# *TaylorActive –* Examining the effectiveness of web-based personally-tailored videos to increase physical activity: a randomised controlled trial protocol

**DOI:** 10.1186/s12889-015-2363-4

**Published:** 2015-10-05

**Keywords:** Physical activity, Web-based, Online, Internet, Computer-tailoring, Text-based, Video-based, Intervention, Randomised controlled trial, Behaviour change

## Abstract

**Background:**

Physical inactivity levels are unacceptably high and effective interventions that can increase physical activity in large populations at low cost are urgently needed. Web-based interventions that use computer-tailoring have shown to be effective, though people tend to ‘skim’ and ‘scan’ text on the Internet rather than thoroughly read it. The use of online videos is, however, popular and engaging. Therefore, the aim of this 3-group randomised controlled trial is to examine whether a web-based physical activity intervention that provides personally-tailored videos is more effective when compared with traditional personally-tailored text-based intervention and a control group.

**Methods/design:**

In total 510 Australians will be recruited through social media advertisements, e-mail and third party databases. Participants will be randomised to one of three groups: text-tailored, video-tailored, or control. All groups will gain access to the same web-based platform and a library containing brief physical activity articles. The text-tailored group will additionally have access to 8 sessions of personalised physical activity advice that is instantaneously generated based on responses to brief online surveys. The theory-based advice will be provided over a period of 3 months and address constructs such as self-efficacy, motivation, goal setting, intentions, social support, attitudes, barriers, outcome expectancies, relapse prevention and feedback on performance. Text-tailored participants will also be able to complete 7 action plans to help them plan what, when, where, who with, and how they will become more active. Participants in the video-tailored group will gain access to the same intervention content as those in the text-tailored group, however all sessions will be provided as personalised videos rather than text on a webpage. The control group will only gain access to the library with generic physical activity articles. The primary outcome is objectively measured physical activity. Secondary outcomes include website engagement and retention, quality of life, depression, anxiety, stress, sitting time, sleep and psychosocial correlates of physical activity. Outcomes will be measured at baseline, 3, and 9 months.

**Discussion:**

This study presents an ideal opportunity to study the effectiveness of an isolated feature within a web-based physical activity intervention and the knowledge generated from this study will help to increase intervention effectiveness.

**Trial registration:**

Australian New-Zealand Clinical Trial Registry: ACTRN12615000057583. Registered 22 January 2015.

CQUniversity Ethics Project Number: H14/07-163

## Background

To prevent chronic disease, 30 minutes a day of moderate intensity physical activity has substantial positive effects on health and wellbeing [1, 2]. Yet, only 46 % of Australians meet the National Physical Activity Guidelines [3, 4]. This level of inactivity is costing Australia an estimated $1.6 billion in health care costs every year [5]. To change the prevalence of inactivity and make a considerable impact on population health interventions are needed that can reach a large number of people, change behaviour effectively (in short- and long-term) and be affordable when implemented in large populations. While this is a significant challenge, web-based interventions have considerable potential to achieve good outcomes in this context [6]. Over 80 % of Australians have access to high-speed broadband connections, and nearly 80 % of those use the Internet everyday [7]. This large uptake has virtually erased the traditional socio-demographic differences in Internet access (age, gender, education), and while a ‘digital divide’ may persist for certain population subgroups it is rapidly declining [7]. Therefore, the Internet is one of the most powerful media for reaching and connecting with people.

To date, numerous web-based physical activity interventions have been evaluated, however they predominantly demonstrate short-term effectiveness in increasing physical activity [6, 8]. Many studies report rapid declines in website usage as the interventions progress, which limits their long-term effectiveness [9, 10]. Low levels of website interactivity are also suggested to explain the modest participant engagement and retention rates in these studies [11, 12]. Websites that provide ‘tailored’, or individually adapted feedback about physical activity are highly interactive and show good effectiveness [13–15]. Compared with generic information users find tailored information more interesting and engaging because it is personally relevant [13]. Computer-tailored interventions can provide large numbers of people with individualised behaviour change information at low cost [15]. Compared with generic messages, tailored messages are more likely to be read and remembered, saved, and discussed with others [14].

Website intervention content is commonly presented as text-based information; this is problematic as there is evidence that text-based information is not effectively transmitted via the Internet. People do not fully read text-based information on the Internet, but rather ‘scan’ and ‘skim’ the content [16]. Internet-based reading behaviour is characterised by more time spent on browsing and scanning, keyword spotting, non-linear reading and more selective reading, while less time is spent on in-depth and concentrated reading [16, 17]. An eye-tracking study concluded that people did not read websites as they would read a book or newspaper. Instead, participants quickly scanned websites in an F-shaped pattern, in which they primarily focussed on the top-left quadrant of the page, and this was consistent across many different types of websites [18].

With the rise of broadband Internet connections, web-based video has become an increasingly popular part of users’ online experiences and it will soon surpass television as the most popular vehicle for delivering video-based content [19]. For example, 71 % of adults use video-sharing websites such as *YouTube* and 28 % of adults accesses these sites daily [20]. Videos have been used in previous health behaviour change websites; however their contents have not been tailored to individual recipients, mainly because the videos were merely supporting other intervention components [21–23]. Pilot studies that informed the current study by Soetens et al. [24] and Alley et al. [25], have demonstrated initial efficacy for using tailored videos, with participants in the video group rating the acceptability of the advice significantly higher than those receiving text-based feedback; they also spent significantly more time on the website. However, the methodological limitations of these studies (e.g. subjective measures, short follow-up periods, under powered samples) require that these outcomes be confirmed in an adequately powered and methodologically sound randomised controlled trial.

To fully harness the potential of computer-tailored websites they will need to be implemented in a new way. Popular websites are not only highly interactive, but they also provide most of their content in a visually attractive and engaging format (images or video). Health promotion websites are competing for attention with more popular websites, and to be successful, these sites will need to be equally interactive and engaging. Therefore, the current study will examine the effectiveness of a web-based physical activity intervention that provides personally-tailored videos and compare it to traditional personally-tailored text-based information and a control group. Secondary study aims are to examine mediators (e.g. psycho-social correlates) and moderators (e.g. socio-demographics) of intervention effectiveness, as well as to examine between group differences in changes to quality of life and participant engagement and retention.

## Methods

### Participants

Eligible participants will be adults who have broadband Internet access, speak and read the English language, live anywhere in Australia, and fail to meet existing national physical activity guidelines of engaging in 150 minutes of moderate to vigorous physical activity over five or more days of the week [26]. The ‘Physical Activity Readiness Questionnaire’ (PARQ) will be used to assess whether potential participants can safely increase their physical activity levels [27]. If this is not the case, and without prior medical clearance, they will be excluded from the study, as will pregnant women, those with a BMI under 17.5 and people with a self-reported physical impairment preventing them from being or becoming more physically active. This study has been approved by the Central Queensland University Human Ethics Committee (H14/07-163), and complies with the Helsinki Declaration.

### Recruitment

Five hundred and ten participants will be recruited through social media advertisements (e.g., Facebook), traditional media (e.g., newspaper, radio), e-mail and third-party databases (e.g. www.trialfacts.com). All advertisements will direct interested individuals to a specific recruitment webpage. On this recruitment page more information about the study can be found along with the participant information sheet. If people are interested in participating in the study they will be asked to complete an online screening questionnaire to assess their eligibility. This page will be able to instantly assess whether people are eligible to participate and provide an explanation for those who are not eligible. If eligible, people will additionally be asked to complete an online form to record contact details and provide informed consent with regards to their participation in this study.

### Procedure

When contact details of eligible people are received through the website, a project officer will make contact either through e-mail or phone (according to indicated preference) to verify the information provided. Subsequently, people will receive an Actigraph activity monitor using registered mail, as well as instructions on how to use the device, an Actigraph monitor log, a participant information sheet, and a return post-bag. They will be asked to wear the activity monitor for 7 consecutive days (and nights if comfortable) from the day of receipt. A project officer will contact potential participants to ensure the activity monitor has arrived and that they are wearing the device as instructed. At this time, the project officer will also schedule a time to conduct the self-reported baseline measures. The self-reported baseline measures will be administered via Computer Assisted Telephone Interviewing (CATI) by trained interviewers who are blinded to group allocation from the Population Research Laboratory (PRL) at the Central Queensland University (CQU). The CATI assessment will take approximately 30 minutes to be completed. When the activity monitor with valid data and Actigraph log sheet are returned to the university and the CATI assessment has been completed, participants will be randomised into one of three groups using a randomly generated sequence through freely available software (www.randomization.com). The same measurement procedures will be repeated at 3 and 9 months. These study procedures ensure the collection of high quality data without face-to-face contact. This better represents the reality of using health promotion websites and allows that participants can live anywhere in Australia.

### Study Design

This is a three group randomised controlled trial with assessments at baseline, 3 months and 9 months (see Fig. 1). The same website will be used for all groups, but it will be programmed so that it only provides participants with access to the intervention features related to their allocated group. All groups will gain access to a static text-based library that contains generic physical activity information. The control group will only receive access to this library and will not have access to any other intervention features. Findings from previous studies indicate that static websites providing generic information are not effective in increasing physical activity, and can thus act as a control intervention [28]. In addition to having access to the generic library of articles, the ‘text-tailored’ group will have access to eight personally-tailored physical activity sessions that are delivered as personalised text on a webpage over a three-month period. The ‘video-tailored’ group will receive the same eight personally-tailored physical activity sessions, however they will be delivered as personalised videos. The videos will be released at the same schedule as the tailored text in the text-tailored group. All groups will receive regular reminders to return to the website at an identical schedule to control for the amount of contact between groups. This study is specifically designed to isolate the effect of video-tailoring and compare it with a text-tailored group and a control group. Using the same web-based platform for all groups ensures that website usage between groups is not confounded by non-specific website elements such as design, readability, usability and user-friendliness, as these may differ when using different websites and influence actual usage [29]. Having a web-based control group ensures that exposure to intervention contents across all groups can be objectively measured through website-usage statistics.

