### Intervention

#### Intervention content

**Library:** The intervention library is populated with 19 brief articles (generally 2 A4 pages in length or shorter) about different aspects of physical activity and what to do to increase physical activity levels. Example topics include: ‘Are you physically fit?’, ‘Getting motivated’, ‘What is a healthy weight?’, ‘Making time to be active’, ‘Get started walking’, ‘Tips and tricks’, and ‘Why be active?’. Each article can be rated by users by way of a ‘5 star’ system and the most popular articles are displayed at the top of the list. The articles can also be downloaded as a PDF-file. This generic content is available for participants in all groups.

**Personally tailored feedback:** As the intervention content provided for the text-tailored and video-tailored groups is identical it will be described in one section for both groups. To generate the personalised content, participants are asked questions about how active they have been the previous week in conjunction with questions relating to individual, social, environmental and theory-based correlates of physical activity behaviour. Based on the answers of participants, and through applying IF-THEN algorithms, personally relevant physical activity content is automatically selected from a database. In this study, eight sessions with personalised feedback will be provided to participants, hence participants will need to complete eight brief surveys before receiving feedback. The website stores answers to previous sessions, and therefore, is able to provide feedback on progress towards meeting goals. The eight sessions are organised in a set order and the ‘next’ session can only be accessed when the ‘previous’ session has been completed. All sessions are released at a set time point and if participants do not access newly available sessions, they will receive up to 3 reminder e-mails and a phone call from project staff. When a session is made available participants can complete it as many times as they like, however the session will be ‘locked’ when the next session becomes available. Personal feedback from past sessions will be accessible throughout the intervention but it cannot be changed. This locking of session is needed to produce progress feedback that is credible (e.g., the changing of original ‘baseline responses’ would make future progress feedback incorrect).

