## Discussion

This study presents an ideal opportunity to study the effectiveness of a specific component within a web-based physical activity intervention. In recent years a growing number of randomized controlled trials have examined the effects of web-based health behavior change interventions [6, 8]. However, these interventions usually have a plethora of different intervention components making it impossible to attribute effectiveness to specific elements within the intervention [62]. Without more knowledge of what components do and do not work, it will be difficult to make progress and improve intervention effectiveness. Previous studies have emphasized the need for research examining the effectiveness of intervention components in isolation [63], and this is what our study will do. As such, we expect that the findings from this study will provide increased understanding of the benefits of new web-based technologies. It is anticipated that the personalized videos will be more engaging compared to personalized text-based information, which will lead to higher overall participant engagement and retention into the intervention. Higher participant engagement has shown to result in higher levels of behavior change [64] and ultimately this will lead to improved health outcomes. Strengths of our study are the use of objective measures to assess physical activity outcomes and web-usage outcomes, a large sample size with sufficient analytical power, a standardized exposure and contact across groups, no face-to-face contact with participants which better mimics real implementation of web-based interventions, and numerous measures to assess secondary outcomes, such as for example: ‘how do environmental attributes moderate intervention effectiveness?’.

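### Contact is presented as equalised across the three groups, but e-mails and a staff call are triggered by unopened tailored sessions, which the control group does not have

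*Protocol article*

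**What the plan says.** Three places in the protocol article bear on contact.

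- **Study Design** gives a rule for everyone, with its purpose: "All groups will receive regular reminders to return to the website at an identical schedule to control for the amount of contact between groups". The same section says of control: "The control group will only receive access to this library and will not have access to any other intervention features".
- **Intervention content**, under the personally tailored feedback, gives a second rule: "if participants do not access newly available sessions, they will receive up to 3 reminder e-mails and a phone call from project staff". The opening of that description limits it to two of the three groups: "As the intervention content provided for the text-tailored and video-tailored groups is identical it will be described in one section for both groups". It also says that "eight sessions with personalised feedback will be provided to participants", and that sessions are gated: the next "session can only be accessed when the" one before it has been completed.
- **Discussion** lists among the strengths "a standardized exposure and contact across groups".

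On timing, Study Design adds: "The videos will be released at the same schedule as the tailored text in the text-tailored group". The article states no prompt or call rule tied to control participants' use of the library.

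**The concern.** The first rule is justified by equal contact, and the Discussion relies on it. The second rule makes contact depend on not opening something that only the tailored groups have. A control participant has no session to miss, so the trigger as written cannot fire in that group.

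Two comparisons are touched, in different ways.

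- **Tailored versus control.** Statistical Analyses compares each intervention group with control. If e-mails and staff calls go only to the tailored groups, part of any difference in physical activity or website use could come from the prompting and not from the tailored content. Study Design presents the trial as isolating video-tailoring, and the equal-contact statement supports that reading.
- **Video versus text.** The rule is the same in both groups, but the contact a participant receives depends on that participant's non-access. The Discussion expects video to engage more. If it does, text participants would draw more prompts, which would tend to bring the two groups closer on logins, sessions completed and retention. The Abstract lists engagement and retention as secondary outcomes.

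**Working it through.** The plan gives no figure for contact, so there is none to reproduce. The check sets the rules side by side and then counts what the triggered rule can produce.

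**Step 1: do the rules give equal contact?** Take the two possible readings of the Study Design reminders.

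1. *They are a separate stream common to all groups.* The session-triggered e-mails and call then come on top of that stream, in the tailored groups only. The schedule of the common stream is identical; the amount of contact is not.
2. *They are the same reminders that Intervention content describes.* Control then needs a counterpart trigger, and none is stated. Even a login-based counterpart would make contact follow each participant's engagement, so the amount would not be fixed.

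Neither reading, as written, yields the equal amount of contact that Study Design gives as its purpose.

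**Step 2: inputs for the count.**

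- Sessions: 8 in each tailored group (Intervention content), 0 in control (Study Design).
- Contacts when sessions are not accessed: up to 3 e-mails and 1 call (Intervention content).

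**Step 3: session-triggered contacts per participant over the 12-week programme.**

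| Group and reading | E-mails | Calls |
|---|---|---|
| Control | 0 | 0 |
| Tailored, every session opened promptly | 0 | 0 |
| Tailored, allowance applies once, or participant stalls at session 1 and is prompted for that session only | up to 3 | up to 1 |
| Tailored, allowance renews at each session and none is opened | 8 × 3 = 24 | 8 × 1 = 8 |

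The article does not say whether the allowance renews. Because of the gating, someone who never completes session 1 may never have a later session to miss. The last row is therefore a ceiling, not an expectation.

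**Step 4: how contact moves with non-access, on the renewal reading.** The share of sessions missed, *p*, is an assumption; the article gives no value. Two variants bracket the way the contacts could follow one another:

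- Variant A: every missed session draws the full set. E-mails = 24*p*, calls = 8*p*.
- Variant B: contacts are sequential, and *p* is also the chance that each e-mail fails to bring the participant back. E-mails = 8(*p* + *p*² + *p*³), calls = 8*p*⁴.

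| *p* | A: e-mails | A: calls | B: e-mails | B: calls |
|---|---|---|---|---|
| 0.25 | 6 | 2 | 2.6 | 0.03 |
| 0.50 | 12 | 4 | 7.0 | 0.5 |
| 0.75 | 18 | 6 | 13.9 | 2.5 |

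The number of calls in particular depends heavily on details the article does not give. In every row the tailored figure exceeds 0 and rises with non-access.

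**The case against.** **The statements need not contradict each other.** Study Design promises an identical schedule, which is about timing, and a common scheduled stream can run alongside session prompts. Control might also have matched reminders that a condensed article does not describe. This stands to the extent that a reader who infers the two rules cannot both hold goes too far. It does not remove the point: the purpose stated in Study Design is the amount of contact, the Discussion claims standardised contact, and a separate stream leaves the session prompts as an extra in the tailored groups.

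**The control group is not without staff contact.** Under Procedure, project officers contact participants and a telephone interview of about 30 minutes is held at baseline, 3 and 9 months in all groups. Session calls prompt use of the programme and can be seen as part of delivering it. This is fair. It means the tailored-versus-control contrast is a comparison of packages, and it is enough to describe it so. It does not make contact equal.

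**Video versus text is sound.** A reader might infer that differing numbers of prompts confound this comparison. They do not. Both groups have the same rule and release schedule, and prompts received after randomisation are a consequence of engagement. The comparison is valid for each format delivered with that prompting. What remains is a possible narrowing of engagement and retention differences, which matters for interpretation.

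**The large counts are a worst case.** Correct: 24 e-mails and 8 calls should not be cited without the reading that gives 3 and 1.

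**Conclusion.** The concern holds in a limited form. As written, the article does not equalise the amount of contact between the tailored groups and control, although Study Design and the Discussion say or imply that it does. Session-triggered contact is 0 in control. In the tailored groups it lies between 0 and either 3 e-mails and 1 call, or 24 e-mails and 8 calls, depending on whether the allowance renews and how the gating works.

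The conclusion rests on there being no unstated matching rule for control. The size and direction of any bias in physical activity cannot be computed from the document, and nothing in it shows that an effect against control would be due to the prompting. For video versus text, any narrowing of engagement and retention depends on the formats differing in non-access, which the article expects but cannot yet know.

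This should be corrected, at small cost. The trial remains valid as a comparison of packages.

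**What to change.** Reconcile Study Design, Intervention content and Discussion in one of two ways.

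1. Give control a matched prompt and call rule at the same time points, for example prompts to return to the library, and state it.
2. Keep the session-triggered prompts as they are, and withdraw or qualify the statements about an identical reminder schedule and standardised contact. Describe the tailored-versus-control effect as that of tailoring plus session prompting.

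In either case, state whether the allowance of e-mails and a call renews at each session, log every e-mail and call per participant, and report the counts by group so that readers can judge the video–text engagement results with them in view.

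The cost is a contact log, plus a little reprogramming under the first option or somewhat weaker wording under the second. Neither option needs more participants or changes the primary outcome. Fixing all prompts to the calendar, or counting engagement only before the first prompt, would go further; both are debatable design preferences and are not needed to resolve this point.
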